#### Demographic, Social, and Health Characteristics

These will include older adults’ age, sex, marital or partnership status (population registries and RAI-HC), physical disability (ADLh Scale score of >3), and cognitive impairment (CPS score of >3). Available data sets include only a binary variable on biological sex (male or female) and no nonbinary information on gender identity. We will also include RAI-HC measures of caregiver availability (item G1e) and burden (items G2a-c). Finally, we will include 4 publicly available area-level measures from the Canadian Index of Multiple Deprivation [76,77]: residential instability (eg, housing insecurity, overcrowding, and frequent moves), economic dependency (high number of older adults, children younger than 15 years, and persons receiving government transfers), ethnocultural composition (eg, immigrants and racialized individuals), and situational vulnerability (eg, indigenous peoples, dwellings needing major repairs, and low education). Using Statistics Canada data, each measure is derived for 54,775 geographical dissemination areas, using 17 variables. Quintile-based ranks for each of the indices (1=least deprived to 5=most deprived) will be assigned to individuals based on their home’s postal code [77].

#### Propensity Score–Matching Variables

To compare outcomes between day program attendees and nonattendees, we will use propensity score matching [78] (for details, see Statistical Analyses section). Propensity scores aim to ensure a similar distribution of baseline variables among treatment (day program attendees) and control (nonattendees)—akin to what random assignment aims to accomplish in randomized trials [78]. Since we lack evidence on differences between day program attendees and nonattendees, our objective 2 analyses will be key to informing the selection of the exact covariates that will form the propensity score. We will derive covariates for day program attendees from the RAI-HC day program eligibility assessment (index date). For each day program attendee, we will identify potential matches as nonattendees whose first RAI-HC assessment was completed within ±3 months of the attendee’s index date (ie, admission to long-term home care at about the same time). This RAI-HC assessment will provide the relevant covariates to enable propensity score matching with day program attendees as of their index date.

Our first set of matching covariates will be RAI-HC variables used by health systems to determine day program eligibility [60,65,66]: physical functioning (ADLh Scale), cognition (CPS), behavioral symptoms (Aggressive Behavior Scale [79]), bladder or bowel continence (items I1, I3), availability of a caregiver (item G1e), and caregiver distress (items G2a-c). This will ensure that control participants are potentially eligible to a day program. Possible reasons for nonattendance include the lack of day program spaces, preference not to attend, inability to afford the required copayments, or not receiving a day program referral. Our experts assure us that the pool of potential matches far exceeds that of attendees, supporting the feasibility of this study and underscoring the lack of day program spaces. This approach excludes individuals whose care needs are either too low or too severe for day program eligibility, but it minimizes confounding by the matched variables and ensures comparable groups at baseline [80-82]. Finally, we will include a second set of matching covariates: health and social characteristics identified in objective 2 by which attendees and potentially eligible nonattendees differ and that overlap sufficiently between attendees and nonattendees (eg, age, sex, type or duration of publicly funded community care received before the matching index date, and deprivation indices).

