### Data Sources

For each individual in our cohort, designated provincial health system analysts will link all records available within the study time frame from the following databases: (1) regional continuing care registries, documenting when an individual starts or stops receiving any community-based continuing care, including day programs, how these services change over time, and when an individual is admitted to a care home. (2) Population registries for each participant’s demographic data. (3) RAI-HC assessments [64], completed annually for people receiving long-term home care (60+ days), and to determine day program eligibility. The RAI-HC will provide data on older adults’ medical conditions, functional dependence, pain, cognitive impairment, mood, and behavioral problems. It also includes information on a person’s marital or partnership status, caregiver availability, whether that caregiver lives with the older adult, and caregiver distress. Additional caregiver characteristics are not included in the available provincial databases, posing a limitation to our quantitative analyses. However, a related prospective cohort study that we are conducting in Ontario will allow us to link comprehensive caregiver and older adult data, and we are currently conducting additional qualitative research that will illuminate how caregiver characteristics may affect day program use and outcomes. (4) Discharge abstract database (DAD) for information on all inpatient hospital stays, including diagnoses and length of stay. (5) National Ambulatory Care Report System (NACRS) for all emergency department visits and diagnoses. In British Columbia, we will use the physician payment file in addition, since NACRS is not collected in all emergency departments [70]. (6) Pharmaceutical information on outpatient prescription medications filled through a community pharmacy and covered by provincial drug formulary. (7) Care provider claims data for health service claims submitted for payment by health care providers (eg, general practitioners, nurse practitioners, geriatricians, geriatric psychiatrists, neurologists, therapists) to obtain information on general and specialist health services used by participants.

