### Study Variables

#### Exposure

Our exposure will be different patterns of day program use or nonuse, based on information from the provincial continuing care registries, documenting the dates a person starts or stops attending a day program, days of attendance, and the duration of each visit. Day program use patterns will be determined, using LCAs (see *Statistical Analyses* section) [71]. We will categorize three continuous variables as low, low-moderate, high-moderate, or high use, using sample distribution quartiles: (1) time between first RAI-HC assessment and first attendance of a day program; (2) average number of hours of day program attendance (ie, total number of hours spent in a day program divided by the number of times attended); and (3) total number of days a person attended a day program. LCAs will also include a categorical variable, indicating whether a person consistently attended a day program or whether there were longer periods (several weeks) of nonattendance. Nonuse will be defined as no day program exposure at any time during a person’s continuing care trajectory.

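### Controls are matched only at their first RAI-HC but attendees at an eligibility RAI-HC that may be a reassessment, so time since entry to assessed home care can differ between the groups

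*Protocol article*

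**What the plan says.** All references are to the Protocol article, Methods.

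- **Attendees** (Propensity Score–Matching Variables): "We will derive covariates for day program attendees from the RAI-HC day program eligibility assessment (index date"). Nothing requires this to be the attendee's first RAI-HC.
- **Controls** (same section): "we will identify potential matches as nonattendees whose first RAI-HC assessment was completed within ±3 months of the attendee’s index date". Their covariates come from that same assessment: "This RAI-HC assessment will provide the relevant covariates to enable propensity score matching with day program attendees as of their index date".
- **Rationale for the window** (same section): "ie, admission to long-term home care at about the same time".
- **Repeat assessments** (Data Sources): the RAI-HC is "completed annually for people receiving long-term home care (60+ days), and to determine day program eligibility".
- **Lag to attendance** (Exposure): "time between first RAI-HC assessment and first attendance of a day program" is one of the variables cut at quartiles to define use patterns.
- **Possible safeguard** (Propensity Score–Matching Variables): a second covariate set may include "type or duration of publicly funded community care received before the matching index date". It is given as an example, and covariates in that set are used only if they are ones "that overlap sufficiently between attendees and nonattendees".
- **Time origin** (Study Outcomes): the care home outcome is described as the interval from first RAI-HC to admission.

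**The concern.** The rule fixes time since first RAI-HC at zero for every control and leaves it unrestricted for attendees. An attendee whose eligibility was assessed at a reassessment has already spent time in assessed home care without entering a care home. The matched control has only just arrived. Matching on function, cognition, behavior, continence and caregiver items balances measured status on the index date. It does not balance time in care, or the fact of having remained at home so far.

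Every objective 3 comparison rests on this matched cohort: care home admission, service use, decline and mood. If time in care predicts these outcomes, the groups differ before any program effect. A large sample makes such a bias look more precise without reducing it.

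**Working it through.** **1. The rule against its rationale.** Let E be the date of first RAI-HC and I the index date. For controls, I = E. For attendees, I = E + L, with L ≥ 0. The window requires the control's E to lie within ±3 months of the attendee's E + L. The two entry dates therefore differ by L, give or take 3 months. Entry at about the same time follows only if L is near zero. Data Sources allows L > 0, because the RAI-HC is repeated annually and is also done for eligibility. No section restricts attendees to L = 0 or lets a control be matched at a reassessment.

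**2. Prior-care duration as a safeguard.** Controls are at the start of RAI-HC-assessed care, so their overlap with long-standing clients is poor. If the variable is left out for lack of overlap, the imbalance stays. If it is kept, the caliper (0.2 SD of the logit) tends to discard later-starting attendees, and the matched sample drifts toward people who attend from entry.

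**3. Size under no program effect.** The documents give neither the distribution of L nor an admission hazard, so there is no plan figure to reproduce and all inputs here are assumptions. They are: L exponential with mean 0.5, 1 or 2 years; death 0.15 per year; 5-year follow-up; 15,000 people per group; unadjusted Cox model. The admission hazard is h(t) = h0 + (h1 − h0) × min(t, 3)/3, with t in years since first RAI-HC. True HR = 1.

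| Clock | Hazard per year | L = 0.5 | L = 1 | L = 2 |
|---|---|---|---|---|
| Index date | rising 0.06 to 0.18 | 1.11 | 1.18 | 1.24 |
| Index date | falling 0.18 to 0.06 | 0.88 | 0.80 | 0.73 |
| Index date | rising 0.10 to 0.14 | 1.04 | 1.03 | 1.08 |
| Index date | constant | about 1 | about 1 | about 1 |
| First RAI-HC, no delayed entry | rising 0.06 to 0.18 | 0.87 | 0.78 | 0.57 |
| First RAI-HC, no delayed entry | constant | 0.86 | 0.71 | 0.50 |

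Repeat runs moved single entries in the first two rows by up to 0.04. Across the threefold-rising, threefold-falling and constant shapes, the first-RAI-HC clock without delayed entry gave 0.44 to 0.90. With delayed entry at the index date it gave 0.95 to 1.03.

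**4. Hand check of the last row.** Assume a constant admission hazard of 0.12, the midpoint of 0.06 and 0.18. The total exit rate is 0.12 + 0.15 = 0.27 per year. Mean follow-up from index over 5 years is (1 − e^(−0.27×5))/0.27 = (1 − 0.259)/0.27 = 2.74 years. Counting from first RAI-HC adds L event-free years to each attendee, so the crude rate ratio is 2.74/(2.74 + L):
- L = 0.5: 2.74/3.24 = 0.85
- L = 1: 2.74/3.74 = 0.73
- L = 2: 2.74/4.74 = 0.58

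The direction and rough size agree with the simulated 0.86, 0.71 and 0.50. This is immortal time: attendees cannot be admitted before their own index date. For comparison, Sample Size Calculation plans on a hazard ratio of 0.6.

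**5. A different hazard model.** A Weibull time to admission (scale 6 years, 3-year follow-up) with the same mean lags gives 1.10, 1.20, 1.29 (shape 1.3) or 1.17, 1.36, 1.51 (shape 1.6) on the index clock. On the first-RAI-HC clock, across shapes 1.0 to 1.6, it gives 0.82–0.88, 0.68–0.79 and 0.52–0.60.

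**6. Late index dates.** First RAI-HCs end on December 31, 2021, so an attendee indexed more than 3 months later has no eligible control. With entry uniform over 2012–2021 and mean lags of 0.5 to 3 years (both assumed, ignoring exits before index), this affects 3% to 18% of attendees.

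**The case against.** Four points can be made for the plan.

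- **Extent.** A reader might infer that many attendees are affected, because the lag to attendance varies enough for quartiles. The documents do not support that. The lag in Exposure runs to first attendance, so it can include waiting for a space after eligibility, and lack of spaces is a listed reason for nonattendance. Data Sources shows only that a later eligibility assessment is possible. This stands: the share is unknown and could be small.
- **Balance.** A reader might infer that prior-care duration cannot be balanced at all. That is too strong. The covariate is publicly funded community care of any type, the registries record when any such care starts, and controls may have had some before their first RAI-HC. Poor overlap is a fair expectation; none is not shown. If the caliper did enforce balance, the harm would be a narrower population and not confounding by duration.
- **Magnitude.** A threefold hazard change has no source in the documents, and the milder rise gives only 1.03 to 1.08 on the index clock. The simulations also omit the matching covariates and time-varying adjustment, which would capture part of why hazard changes with time in care. This stands: the figures are illustrations, not estimates of the plan's bias.
- **Clock.** A reader might infer one direction of bias. The article describes the outcome from first RAI-HC but does not say when follow-up enters the model. With delayed entry the null ratios are close to 1, and without it they favour attendees. The direction cannot be read from the text.

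None of this repairs the rule. The article itself fixes the asymmetric index dates and attaches a rationale that holds only when L is near zero.

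**Conclusion.** The point holds for attendees whose eligibility assessment is not their first RAI-HC, a share the documents do not give. For them the groups differ in time since entry to assessed home care, and the stated reason for the ±3-month window does not apply. Attendees assessed for eligibility at their first RAI-HC are unaffected.

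Under the assumed mean lags of 0.5 to 2 years and no true effect, the hazard ratio is about 1.1 to 1.25 (threefold rising hazard), about 0.75 to 0.9 (threefold falling) or about 1 (constant) with the clock at the index date. It is about 0.45 to 0.9 with the clock at first RAI-HC and no delayed entry, a range that includes the planned 0.6. Sign and size therefore depend on lag, hazard shape and clock. Because the sign is undetermined, the bias could not be allowed for after the fact, so the rule should be changed before matching starts.

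**What to change.** - Delete the word first from the control-matching rule. Let any RAI-HC, first or reassessment, within ±3 months of the attendee's index date serve as the control's index, provided the person is still at home and unexposed at that date.
- Match on time since first RAI-HC in bands, for example under 6, 6–12, 12–24 and over 24 months.
- Use the matched index date as time zero for both groups, or keep first RAI-HC as the origin with delayed entry at the index date. Reconcile Study Outcomes with the choice.
- Settle future attendees. Exposure defines nonuse as no attendance at any time. Either keep that definition for controls or, if people not yet attending are admitted as controls, state that they are censored at first attendance.
- Correct the explanatory remark about simultaneous admission to home care.

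Cost: more work in the shared matching program, using reassessments that are already to be linked. The candidate pool grows, since one person can qualify at several dates but is used once. Some matches may be lost where no reassessment falls near the index date: Sample Size Calculation says about 50% are reassessed within 12 months and another 10%–30% after more than 15 months.

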### Setting and Sample

Our study settings are community-based continuing care systems. Each province provides access to a range of publicly funded community-based continuing care services, including adult day programs [55-63]. Each provincial health system determines and enacts access criteria and provides services (directly or via contracted providers) [55-63]. Day program eligibility is assessed in each province, using comparable processes, criteria, and assessments (ie, the Resident Assessment Instrument—Home Care [RAI-HC], a standardized, valid, reliable assessment tool [64]) [60,65,66]. To be eligible, attendees need to have not only some care dependency but also the ability to cope to some extent with activities of daily living, ambulate or transfer with no or minimal assistance, be continent or independent in managing continence products, exhibit no or easily manageable responsive behaviors, and either be alone for extended periods or have a caregiver who requires respite. Our study cohort will include all individuals aged 65 years or older with an initial RAI-HC assessment completed between January 1, 2012, and December 31, 2021. We will follow everyone until they move into a care home, are lost to follow-up (eg, because of death, moving out of province, loss of public insurance eligibility), or until December 31, 2024 (the end of the period covered by our data). That will allow for a care trajectory of at least 3 years (for those with an initial RAI-HC assessment in December 2021), enabling us to assess the number and characteristics of individuals with different day program use patterns, and compare them with those who were never exposed to a day program.

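### Controls need a first RAI-HC within ±3 months of the attendee's index date, but no cohort member has a first RAI-HC after December 31, 2021, so attendees indexed after March 31, 2022 cannot be matched for objective 3

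*Protocol article*

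**What the plan says.** Setting and Sample limits the cohort to people aged 65 or older with an "initial RAI-HC assessment completed between January 1, 2012, and December 31, 2021". They are followed to care home entry, loss to follow-up, or "until December 31, 2024 (the end of the period covered by our data". The entry window is the same for attendees and nonattendees.

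Propensity Score–Matching Variables sets the attendee's starting point: "We will derive covariates for day program attendees from the RAI-HC day program eligibility assessment (index date"). Potential matches are "nonattendees whose first RAI-HC assessment was completed within ±3 months" of that date.

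Two other statements show that the eligibility assessment need not be the first RAI-HC. Data Sources describes the RAI-HC as "completed annually for people receiving long-term home care (60+ days), and to determine day program eligibility". The examples of matching covariates include "type or duration of publicly funded community care received before the matching index date".

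The Objective 3 analysis section specifies one-to-one matching without replacement within a caliper, with propensity score quintiles as the fallback if the matched sample is too small.

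**The concern.** The attendee is anchored on an assessment that may fall at any point in follow-up. The control is anchored on a first assessment that cannot fall after 2021. For attendees indexed late, the two rules together leave no one to match.

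The loss is not random. To be indexed after March 31, 2022, a person who entered on December 31, 2021 needs a lag of just over 3 months from first RAI-HC to eligibility, and earlier entrants need correspondingly longer lags. Those removed are the longer-lag attendees of each entry year, most heavily in the last entry years. Assuming that attendance follows eligibility, they also started late. Objective 3 models outcomes by use class, and one variable defining the classes is "time between first RAI-HC assessment and first attendance of a day program". The matched attendees may therefore represent late-start classes less well than the attendees described under objectives 1 and 2.

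**Working it through.** **The plan's own figure.** Setting and Sample states a care trajectory of at least 3 years for the last entrants. December 31, 2021 to December 31, 2024 is 3.0 years, so the dates are being read as intended.

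**Cut-off dates.**
- Latest possible first RAI-HC of any control: December 31, 2021.
- Latest index date with any candidate: December 31, 2021 + 3 months = March 31, 2022.
- Latest index date with a complete ±3-month window: September 30, 2021. From October 2021 the window is truncated. By the end of December 2021 only its earlier half remains, and it shrinks to nothing by the end of March 2022.
- Period with an empty pool: April 1, 2022 to December 31, 2024, which is 33 of 156 months, or 1006 of 4749 days (21%). This is calendar time, not a share of attendees. With entry closed in 2021, new index dates should thin out over these months.

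**Does the fallback help?** No. Quintiles change how scores are compared. The ±3-month rule decides who is a potential match before any score is used.

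**Share of attendees lost (illustration).** The documents do not give the distribution of the lag from first RAI-HC to eligibility, so these are assumptions: entry uniform over 2012–2021, exponential lag with mean m years, no competing exit. Measure time in years from January 1, 2012. Entry closes at 10, the last matchable index date is 10.25, and data end at 13. For t ≥ 10, the proportion indexed by time t is

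F(t) = 1 − (m/10)·[exp(−(t − 10)/m) − exp(−t/m)]

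and the share lost is [F(13) − F(10.25)] / F(13).

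For m = 1: F(13) = 0.9950 and F(10.25) = 0.9221, so the share lost is 0.0729/0.9950 = 7.3%.

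For people who entered in 2021, replace m/10 by m and exp(−t/m) by exp(−(t − 9)/m).

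| Mean lag (years) | All attendees lost | 2021 entrants lost | Mean lag, kept / lost (years) |
|---|---|---|---|
| 0.25 | 1% | 9% | 0.25 / 0.75 |
| 0.5 | 3% | 26% | 0.48 / 1.24 |
| 1 | 7% | 48% | 0.89 / 2.06 |
| 2 | 14% | 63% | 1.54 / 3.25 |
| 3 | 18% | 68% | 1.95 / 4.05 |

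The last column comes from a simulation of 2 million people under the same assumptions, which also reproduced the shares lost.

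**With competing exit.** Assume death, care home entry or other loss at 0.25 per year. Among those found eligible before exit, the lag is then exponential with mean 1/(1/m + 0.25). For m = 0.5, 1, 2 and 3 the overall loss becomes about 3%, 6%, 10% and 12%.

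**The case against.** The strongest reply is that late indexing is inferred. December 31, 2024 is given as the end of follow-up and data, and no passage says attendees may be indexed until then. The matching section also explains the ±3-month rule as admission to long-term home care at about the same time, which suggests that the authors pictured index dates near home care entry. If the eligibility assessment were always the first RAI-HC, the gap would vanish. This stands as a limit on how common late index dates are. It does not remove the conflict: Data Sources and the matching covariates both allow an eligibility assessment after a period of care, and no stated rule closes indexing.

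Three stronger readings might be inferred, and the article does not support them.
- *That no new attendees appear after early 2022.* The index date is the eligibility assessment, not first attendance. Someone found eligible by March 31, 2022 may first attend later, and matched pairs are followed to December 2024.
- *That the use-pattern variable measures the lag at issue.* It runs to first attendance and so may include waiting after eligibility. The article itself names lack of spaces as a reason for nonattendance. A late index date implies a late start if attendance follows eligibility, but a late start does not imply a late index date. Some late starters stay matchable.
- *That objective 3 becomes underpowered.* The article requires 1327 participants and expects more than 200,000 attendees.

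It is also fair to say that the date mismatch does not by itself bias the attendee–nonattendee contrast among pairs that can be formed. It limits which attendees the result describes.

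**Conclusion.** The point holds as a conflict between two stated rules. Under the entry window and the control definition together, the control window is incomplete from October 2021 and empty after March 31, 2022. These dates follow directly from the article and rest on no assumption beyond an eligibility assessment being able to follow the first RAI-HC, which the article allows.

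The size of the loss cannot be computed from the documents. Across assumed mean lags of 0.25 to 3 years it is about 1% to 18% of all attendees without competing exit, and less with it. The high percentages for 2021 entrants concern one of ten entry years. The consequence is selective loss of late-indexed attendees and a narrower population for objective 3, including for late-start use classes. This should be fixed before the shared matching programs go to the three provinces. It does not threaten the study as a whole.

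**What to change.** In Propensity Score–Matching Variables, define potential controls as cohort members without day program use who have any RAI-HC, first or reassessment, within ±3 months of the attendee's index date and at a similar time since first RAI-HC. Take the control's covariates and time zero from that assessment. Study Outcomes now measures time to care home admission from the first RAI-HC, so the time origin there needs to be aligned.

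Cost: the reassessments are already to be linked for every cohort member through December 31, 2024, so no new data are needed. The matching step becomes somewhat more complex, and late pairs have shorter follow-up. Not every nonattendee will have a reassessment near a given date: the article reports about 50% reassessed within 12 months and another 10%–30% after more than 15 months.

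If this is not adopted, restrict objective 3 explicitly to index dates through March 31, 2022, or through September 30, 2021 if a full window is wanted, and report the number of attendees excluded by use class.

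Do not extend first-RAI-HC entry to 2024 for controls alone. That would bring in people outside the cohort being linked, with less than the 3-year minimum trajectory. Because nonuse means no exposure during the whole trajectory, shorter observation would also classify more future attendees as nonusers.
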